### Functional measurements

*Timed Up and Go test*: The participant starts in a seated position, stands up upon command, walks 3 meters, turns around, walks back to the chair, and sits down. The time stops when the subject is seated.

*Short Physical Performance Battery (SPPB*): This battery of tests evaluates lower extremity functional performance using timed measures of standing balance, a 4-meter walk, and five repetitive chair stands.
^
43
^

*Handgrip strength*: Measures the maximum isometric strength of the hand and forearm muscles. The participant holds the dynamometer in the hand with the arm at a right angle and the elbow by the side of the body. When ready, the participant squeezes the dynamometer with maximum isometric effort for 3-5 seconds. Participants will be instructed to perform the test as fast and hard as possible and verbal encouragement will be provided simultaneously. The highest value out of three contractions will be used for analysis.

### Peak aerobic capacity

The VO
_2_ peak will be determined during an incremental cycling test to exhaustion using a recumbent cycle ergometer following the recommendations of the American College of Sports Medicine,
^
44
^ using a portable and validated gas analyzer.
^
45
^ Blood pressure and heart rate will also be analyzed at rest and during the exercise test.

### Dietary and physical activity assessment

The participants will have to fill a dietary record using image-assisted method over three days (two consecutive weekdays and one weekend day) before and after the supplementation period for estimation of macronutrient intake.
^
46
^ Similarly, participants will answer the Global Physical Activity Questionnaire (GPAQ) to assess their physical activity.
^
47
^

### Blood samples

Blood samples will be collected after an overnight fast (12 h) using a needle and Vacutainer kit and will be immediately centrifuged to obtain plasma (1000 × g for 10 min at 4°C) and erythrocyte fractions (3000 × g for 10 min at 20°C). Both fractions will be frozen at −80°C until further analysis. A portion of venous blood will also be collected in LeukoLOCK™ Total RNA Isolation System for the capture and purification of intact RNA from white blood cells, which will be frozen and stored at –80°C until further processing.

### Clinical, cardiometabolic, and inflammatory blood measurements

Plasma rheumatoid factor (RF) and lipid profile will be determined. Further, plasma interleukin-10, and TNF-α levels will be measured via commercial ELISA assay kits.

### Leukocyte gene expression

cDNA will be prepared by reverse transcription of 1 ug of total RNA, using the SensiFASTTM cDNA Synthesis Kit (Bioline) according to manufacturer’s protocol. RNA quantity and quality will be assessed using a Nanodrop 8000 (ThermoScientific, Wilmington, DE, USA) and an Agilent 2100 BioAnalyzer (Agilent Technologies Inc., Santa Clara, California, USA), respectively. Real-time RT-qPCR will be carried out to quantify the changes in the expression of genes associated with inflammatory pathways and SPM synthesis, including TNF-α, interleukin-1β (IL-1β), IL-6, cyclooxygenase-2 (COX-2), lipoxygenase-5 (ALOX5), lipooxygenase-12 (ALOX12), lipooxygenase-15 (ALOX15), and calcium-independent phospholipase A2 VIA (iPLA2VIA). 18S ribosomal RNA (18SRNA) and glyceraldehyde 3-phosphate dehydrogenase (GAPDH) will be used as housekeeping genes. Data will be analyzed using the ΔΔCt method.

### Synovial fluid extraction

All individuals must obtain medical clearance from their Rheumatologist. RA subjects will attend the laboratory after an overnight fast, without having carried out any type of exercise in the previous 48 hours. Local anesthesia (1% Lidocaine) will be applied to the affected joint and synovial fluid will be obtained by a certified rheumatologist.
^
48
^ Synovial fluid will be immediately placed on ice and aliquoted for specific analyses. All aliquots will be stored at −80°C until use.

### Phospholipid fatty acid composition

Quantitative extraction of total lipids from erythrocytes, plasma, and synovial fluid will be carried out according to Bligh and Dyer
^
49
^ with the addition of BHT. Fatty acid methyl esters (FAMEs) from erythrocytes and plasma will be prepared according to Morrison and Smith.
^
50
^ FAMEs will be extracted with 0.5 mL of hexane. FAMEs will be identified and quantified using a gas-liquid chromatograph (Agilent7890B, Santa Clara, CA, USA) equipped with a capillary column (Agilent HP-88, 100 m × 0.250 mm; I.D. 0.25 μm) and flame ionization detector (FID). Identification and quantification of FAMEs will be achieved by comparing the retention times and the peak area% values of unknown samples to those of a commercial lipid standard (Nu-Chek Prep Inc., Elysian, MN, USA). C23:0 will be used as internal standard (Nu-Chek Prep Inc., Elysian, MN, USA) and data will be processed using the Hewlett-Packard Chemstation software system.

### Analyses of SPMs

Plasma and synovial fluid samples (400 μL) will be analyzed in duplicate for oxylipins by HPLC/MS/MS, as previously described.
^
51
^ Briefly, deuterated internal standards (Cayman Chemicals) will be added to plasma samples and adjusted to pH <3.0 prior to solid-phase extraction using Strata-X-SPE (Phenomenex) columns preconditioned with methanol, followed by pH 3.0 water. Samples will be loaded on the columns, washed, and free SPMs will be eluted with 100% methanol. The eluate will subsequently be dried and resuspended in solvent A (water/acetonitrile/formic acid, 70/30/0.02 v/v/v) for oxylipin analysis by HPLC/MS/MS, using a Luna 5-μm C18 column (100 Å, 250 × 2.0 mm, Phenomenex) on a Shimadzu Nexera XR HPLC, coupled to an ABSciex QTRAP 6500 MS operating in negative mode with electrospray ionization. Oxylipins will be eluted with the following gradient: 100% solvent A between 0 and 1 min, and then solvent B (acetonitrile/isopropyl alcohol, 50/50, v/v) is increased linearly to 25% at 3 min, to 45% at 11 min, to 60% at 13 min, to 75% at 18 min, and to 90% at 18.5 min. Solvent B will then be held at 90% until minute 20, dropped to 0% by 21 min, and held until 25 min. Quantification of oxylipins will be performed using a stable isotope dilution method.

### Statistical analysis

Results will be expressed as mean ± SD. A two-way ANOVA with repeated measures followed by Fisher’s least significant difference post-test for multiple comparisons between groups will be used. Linear regression models will be constructed to examine the association between SPMs and clinical, functional, and health parameters, accounting for participant age, sex, and BMI as covariates. A value of p<0.05 will be considered statistically significant.

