^ has initiated a promising new era of research that could explain the benefits observed after n-3 PUFA supplementation and AEx in individuals with RA. However, whether they are responsible for this adaptive response, also remains to be elucidated.

*Research hypothesis:* N-3 PUFA and AEx will have synergistic effects on disease progression, cardiometabolic health, and quality of life in individuals with RA, and these changes will be associated with SPM production in blood and synovial fluid.

*General aim:* To investigate the effects of n-3 PUFA supplementation and AEx training on disease progression, cardiometabolic health, and quality of life and their association with the plasma and synovial fluid levels of SPMs in individuals with RA.

*Specific aims*:
(1)To compare the effects of n-3 PUFA supplementation, AEx training, and the combination of both on disease progression, cardiometabolic health, and quality of life in individuals with RA.(2)To compare the effects of n-3 PUFA supplementation, AEx, and the combination of both on the plasma and synovial fluid levels of the SPMs in individuals with RA.(3)To examine the relationship between the plasma levels of the n-3 PUFA derived SPMs with systemic disease progression, cardiometabolic health, and quality of life in individuals with RA

To achieve these aims we have designed a randomized, 16-week, placebo-controlled, blinded interventional trial.

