### Study design

This study consists of a 16-week intervention with n-3 PUFAs and/or aerobic exercise (AEx) training. The subjects will be randomly assigned in a double-blinded manner to one of four groups: placebo control (PLA), PLA+AEx, n-3, or n-3+AEx. A stratified randomized assignment (by block) process will be employed to ensure that the experimental groups are balanced for disease activity, pharmacological treatment, sex, and age. The principal investigator and pharmacy personal will be aware of patient allocation and will code the information. Patients and exercise intervention supervisors will be blinded for supplement intervention, while medical specialists and database analysis personal will be blinded for supplement treatment and exercise intervention. The study will be unblinded for patients and medical specialist if the participant worsens their condition according to the criteria described below or if they decide to drop out the study.

The training sessions will be conducted at the Laboratorio de Ciencias del Ejercicio en el Ciclo Vital (Lab-CERVITAL), Universidad de O’Higgins. The week before intervention the participants will perform RA specific tests (e.g., Disease Activity Score-28) and functional measurements (e.g., handgrip strength), peak aerobic capacity test, a dietary and physical activity assessment, and blood samples will be collected. Subsequently, participants will start their 16-week intervention (PLA, PLA+AEx, n-3, or n-3+AEx). At the end of the intervention the same initial measurements, questionnaires, and assessments will be collected. In a subgroup of participants (n=24 in total or n=6 per group) extraction of synovial fluid will be performed before and after the intervention.

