### Primary and secondary outcomes

Primary outcome: Early morning stiffness is one of the main outcomes significantly improved by n-3 PUFA supplementation in RA patients.
^
11
^ Therefore, the difference in the duration (minutes) of early morning stiffness has been selected as the primary outcome to compare the intervention effect in each group after the intervention period.

Secondary outcomes: Other relevant outcomes which allow the assessment of disease progression will be measured, such as the Disease Activity Score-28, DHA-SPMs, tender and swollen joint count, quality of life, grip strength, analgesic use, and TNF-α blood levels.

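### The hypothesis is synergy of n-3 and exercise, but the stated analysis names no n-3 × AEx interaction, and pairwise group comparisons cannot estimate it

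*Protocol article*

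**What the plan says.** - **Hypothesis** (Introduction, research hypothesis): "N-3 PUFA and AEx will have synergistic effects on disease progression, cardiometabolic health, and quality of life in individuals with RA".
- **Aim 1** (Introduction, specific aims) is worded as a comparison: "To compare the effects of n-3 PUFA supplementation, AEx training, and the combination of both on disease progression".
- **Design** (Study design): participants are randomised to "one of four groups: placebo control (PLA), PLA+AEx, n-3, or n-3+AEx". This is capsule (n-3 or placebo) crossed with exercise (yes or no), although the article does not call it factorial.
- **Primary outcome** (Primary and secondary outcomes): the difference in minutes of morning stiffness "has been selected as the primary outcome to compare the intervention effect in each group after the intervention period".
- **Analysis** (Statistical analysis): "A two-way ANOVA with repeated measures followed by" pairwise comparisons of the groups with Fisher's LSD. The significance threshold is p<0.05.
- **Sample size** (Sample size): α 0.05, power 0.8, effect size 0.42 for morning stiffness, at least 18 per group, 22 recruited. The type of effect size and the contrast it refers to are not given.

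The statistical section names neither the two factors of the ANOVA nor an n-3 × AEx term.

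**The concern.** Synergy means that the combination does more than the sum of the two single effects. That is a statement about one interaction contrast. The four arms allow it to be estimated, but the stated analysis does not single it out.

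With n-3, AEx and time there are three factors. A two-way repeated-measures ANOVA with a post-test between groups therefore reads most naturally as group (four levels) by time (two levels). That gives a 3-df omnibus test followed by pairwise differences. The interaction contrast lies inside those 3 df, but neither the omnibus p-value nor any single pairwise difference reports it.

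What is at stake is how the main hypothesis will be judged. If the only results are pairwise p-values, a pattern such as the combination beating each single treatment, or being the only arm to beat placebo, invites a conclusion of synergy. Plain additivity produces both patterns often.

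**Working it through.** **1. What the stated sample size corresponds to.** Read 0.42 as Cohen's f in a one-way ANOVA with 4 groups (3 df), α 0.05, noncentrality λ = f²N.
- 17 per group: λ = 0.42² × 68 = 12.0, power 0.815.
- 18 per group: λ = 0.42² × 72 = 12.7, power 0.840.

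The computed minimum is 17, close to the stated 18. Other readings do not fit: a two-group difference of 0.42 SD needs 89 per group (two-sided), and a 1-df factorial effect at f = 0.42 needs 12. The stated size thus fits a four-group comparison and not an interaction test. This supports the group-by-time reading of the analysis but does not prove it.

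**2. The synergy contrast.** Let I = (n-3+AEx − PLA+AEx) − (n-3 − PLA), in SD units of the analysed outcome.
- SE of a pairwise difference: √(2/n) = √(2/18) = 0.333 SD.
- SE of I: √(4/n) = √(4/18) = 0.471 SD, on 4 × 17 = 68 df.

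A pairwise difference involves two cell means and I involves all four. No pairwise test can stand in for it.

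**3. How often additive effects look like synergy.** Assumptions: normal outcome, equal SD, 18 per group, cell means 0, e, e and 2e (so I = 0), LSD only after a significant omnibus F, 20,000 simulated trials per row. The values of e are illustrative, because the article gives no SD and no effect in minutes.

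| Each single effect e | Only the combination beats PLA | Combination beats PLA and both single arms | Either pattern | Interaction test rejects (two-sided) |
|---|---|---|---|---|
| 0.42 SD | 21% | 10% | 23% | 5% |
| 0.60 SD | 28% | 26% | 40% | 5% |
| 0.84 SD | 15% | 56% | 59% | 5% |
| 1.00 SD | 6% | 75% | 75% | 5% |

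The two patterns overlap and must not be added. At 0.60 SD the unrounded rates are 28.4%, 26.4% and 39.5% for either, so both occur together in 28.4 + 26.4 − 39.5 = 15.3% of trials. With 22 per group, either pattern occurs in 28%, 44%, 68% and 85% of trials for the same four values of e.

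**4. What the interaction test can detect.** Two-sided α 0.05, noncentrality I/√(4/n).
- At 18 per group, the interaction detectable with 80% power is about 1.34 SD (1.21 SD at 22 per group).
- I = 0.42 SD: 0.42/0.471 = 0.89, power 14%.
- I = 0.84 SD: 0.84/0.471 = 1.78, power 42%.
- For 80% power, 0.42 SD needs 179 per group (716 evaluable) and 0.84 SD needs 45 per group (180 evaluable).

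**The case against.** The strongest case on the other side has four parts.

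- **The article is condensed and the factors are unnamed.** If the two ways are n-3 and AEx, the interaction is an ordinary term of the model, and naming a post-test does not discard it. This is fair and limits certainty about the intended model. It does not remove the point: on either reading the article states which follow-up tests will be run and does not identify the interaction as the test of its hypothesis.
- **No rule for declaring synergy is given.** A reader might infer that the investigators will report additive effects as synergy. The documents do not say so. The percentages above are rates of patterns that could be misread, not error rates of a stated procedure.
- **Group comparisons are wanted.** A reader might infer that the four-group test serves no stated purpose. Aim 1 asks for a comparison of n-3, AEx and the combination, and the primary outcome is to be compared by group, so the test and its follow-up do address stated aims. The mismatch is with the hypothesis of synergy.
- **Power.** A reader might infer that the omnibus test is badly underpowered beside a single-df n-3 contrast. The documents do not support that. It would require reading 0.42 in SD units, which does not reproduce the stated sample size, and assuming no exercise effect. Part of any gain would also come from baseline adjustment, which is a separate matter.

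It also stands that an interaction test in a trial of this size has low power. A remedy that hides this would replace one problem with another.

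**Conclusion.** The point holds as a mismatch between the stated hypothesis and the only between-group analysis stated. The hypothesis needs an interaction estimate; the article offers a two-way repeated-measures ANOVA with unnamed factors and pairwise LSD.

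Under additive effects of 0.60 to 0.84 SD per treatment, pairwise patterns resembling synergy appear in about 40% to 59% of trials of 18 per group, against about 5% for the interaction test (about 2.5% in the synergistic direction). These figures rest on assumed effects in SD units, normality and equal SDs. The outcome is recorded in minutes with a ceiling of 180, so they illustrate the size of the risk and do not predict it.

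The design, the primary outcome and the four-group comparisons for Aim 1 are not called into question.

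**What to change.** Amend the Statistical analysis section as follows.

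1. Name the factors: n-3 (yes/no), AEx (yes/no) and time.
2. Prespecify the n-3 × AEx interaction on baseline-adjusted week-16 morning stiffness, or on its change from baseline, as the sole basis for any claim of synergy, reported with its 95% CI. On change scores this is the n-3 × AEx × time term.
3. Keep the four-group comparisons and the cell means for Aim 1. Give the marginal n-3 and AEx effects as a supplement, since they average over the other factor and are hard to interpret if an interaction exists.
4. State the limited precision: at 18 per group about 1.34 SD is detectable with 80% power, and power is about 14% for 0.42 SD. Say that a non-significant interaction is inconclusive and is not evidence of additivity.

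If low power for the main hypothesis is unacceptable, the alternative is to reword the hypothesis as a comparison of n-3, AEx and their combination.

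Either route changes wording only, with no change to randomisation, recruitment or data collection. The price of the first is an openly underpowered test of synergy; the price of the second is giving up the synergy claim. The change should be made before unblinded data are analysed.

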### Sample size

The sample size calculation for this study is based on an α level of 0.05, a power (1-β) of 0.8, and effect size of 0.42 (morning stiffness).
^
11
^ A minimum of 18 participants are necessary per group; however, 22 individuals will be recruited to account for a typical dropout rate of 20% in long-term intervention studies.

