### RA disease progression

*Duration of morning stiffness*: This will be assessed by asking “How long is your morning stiffness from waking until maximum improvement?”.
^
39
^ The duration of morning stiffness will be reported in minutes up to a maximum of 180 minutes.

*Disease Activity Score-28 (DAS28*): Describes the severity of rheumatoid arthritis using clinical and laboratory data. It is composed of the number of swollen joints (total 28), the number of tender joints (total 28), the Westgren erythrocyte sedimentation rate (ESR), and patients’ global disease assessment through a visual analog scale (VAS). The DAS28 has been extensively validated for its use in clinical trials and it is required by the Chilean Ministry of Health.
^
40
^

*Health assessment questionnaire disability index (HAQDI):* This tool evaluates the functional status of RA individuals. It consists of eight sections: dressing, arising, eating, walking, hygiene, reach, grip, and activities, with 2 or 3 questions for each section. Scoring is from 0 (without any difficulty) to 3 (unable to do). The 8 scores of the 8 sections are summed and divided by 8. This questionnaire has been validated to be used among Chilean RA patients.
^
41
^

*Quality of life RA (QOL-RA) scale*: This scale is an RA-specific health-related quality of life instrument consisting of an 8-item scale. Each item starts with the definition of an element to be considered in rating one’s quality of life, followed by a horizontal 10-point scale anchored with 1 (very poor) at one end and 10 (excellent) at the other end. The elements are physical ability, pain, interaction with family and friends, support from family and friends, mood, tension, arthritis, and health. The higher the QOL-RA Scale score, the higher the health-related quality of life. This scale has been validated to be used in the Spanish language.
^
42
^

*Analgesic use*: Analgesic use will be measured using pill counts for paracetamol and NSAIDs.

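### With only a before and an after measurement, the planned repeated-measures ANOVA is valid but less efficient than an ANCOVA adjusted for baseline stiffness

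*Protocol article*

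**What the plan says.** The Statistical analysis section of the protocol article fixes the model for the group comparisons: "A two-way ANOVA with repeated measures followed by" Fisher's least significant difference post-tests between the groups. It names no covariates for this ANOVA. The only covariates mentioned, "accounting for participant age, sex, and BMI as covariates", belong to the separate regressions of clinical and functional measures on the pro-resolving mediators.

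Under Primary and secondary outcomes, "the difference in the duration (minutes) of early morning stiffness has been selected as the primary outcome". The Study design section places one assessment in the week before the intervention and one after it: "At the end of the intervention the same initial measurements, questionnaires, and assessments will be collected". Under RA disease progression, stiffness is "reported in minutes up to a maximum of 180 minutes". Randomisation is stratified so that the groups are "balanced for disease activity, pharmacological treatment, sex, and age" (Study design).

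The Sample size section asks for at least 18 evaluable patients per group and recruits 22, which is 88 in total.

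**The concern.** A repeated-measures ANOVA on two time points uses the baseline value in a fixed way. It subtracts the whole of baseline from the week-16 value, as if the regression slope of one on the other were 1. With equal variances at the two visits the slope is r, which is below 1, so the subtraction adds baseline noise to the comparison. ANCOVA estimates the slope from the data and avoids this.

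Both methods are unbiased under randomisation, so the planned one gains nothing in return for its larger variance. With 18 evaluable patients per group and baseline stiffness already collected, precision on the primary outcome is given up without need. The stratification factors raise a second, smaller matter: an analysis that conditions on the factors used to stratify follows the design more closely than one that ignores them.

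**Working it through.** **Inputs.** From the article: two assessments (Study design); 18 evaluable per group, so 4 × 18 = 72 (Sample size); α 0.05, power 0.8 and effect size 0.42 (Sample size). Assumed: a two-sided or F test; equal outcome variance s² at both visits; r between 0.3 and 0.8, since the article gives neither an SD nor a correlation; and, for the word "two-way", group and time as the two factors, which the article does not name.

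**The plan's own figure.** Read as Cohen's f in a one-way ANOVA of four groups, 0.42 needs N = 66, or 17 per group (power 0.815 at 17 and 0.840 at 18). That is close to the stated 18. Read as a standardised mean difference between two groups, 0.42 needs 89 per group, and power at 18 is 0.24. The stated 18 therefore fits only the first reading, and even then approximately.

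**Variances.** With two visits, the group-by-time F test is the same as a one-way ANOVA on week 16 minus baseline.

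- Change score: Var = s² + s² − 2rs² = 2(1−r)s²
- ANCOVA on baseline: Var = (1−r²)s² = (1−r)(1+r)s²
- Ratio, ANCOVA to change: (1+r)/2, below 1 for every r below 1

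| Assumed r | Change, 2(1−r) | ANCOVA, 1−r² | Ratio | SE smaller by | 18 per group worth |
|---|---|---|---|---|---|
| 0.3 | 1.40 | 0.91 | 0.65 | 19% | 28 |
| 0.5 | 1.00 | 0.75 | 0.75 | 13% | 24 |
| 0.7 | 0.60 | 0.51 | 0.85 | 8% | 21 |
| 0.8 | 0.40 | 0.36 | 0.90 | 5% | 20 |

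The last column is 18 divided by the ratio. As a gain in patients, 1/ratio − 1 is 54%, 33%, 18% and 11%. Baseline adjustment costs 1 of 72 − 4 = 68 residual degrees of freedom.

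**Power, illustrative only.** Three settings, each at r = 0.3, 0.5, 0.7 and 0.8:

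- If the group-by-time test has exactly 80% power at N = 72, ANCOVA has 94.5%, 90.8%, 86.5% and 84.4%.
- For a pooled n-3 contrast of 36 against 36 with 0.42 taken as an SD unit (SE = SD of the analysed quantity × √(1/18), non-central t), power rises from 32% to 45%, 42% to 53%, 62% to 69% and 79% to 83%.
- In a simulation of 4,000 trials per setting, 18 per group, with assumed effects of 0, 0.42, 0.42 and 0.84 SD, power was 0.38 against 0.55, 0.51 against 0.65, 0.76 against 0.82, and 0.91 against 0.93. Type I error lay between 0.047 and 0.053 for both methods.

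**Stratification factors.** Adding four degrees of freedom (one per factor, assumed) to the ANCOVA in the first setting leaves 68 − 1 − 4 = 63. If the factors explain none of the remaining variance, power falls by at most about 0.2 points. If they explain 5%, it rises by about 1 to 2 points; if 10%, by about 2 to 4 points.

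**The case against.** The strongest reply is that the planned test is conventional and valid, that the primary outcome is itself worded as a difference, and that a condensed article may leave its covariate list to a fuller document. Much of this stands. Type I error is held, and silence on covariates for the ANOVA is not a decision to exclude them. It does not remove the core, because the choice of repeated-measures ANOVA is stated, and it is that choice which fixes how baseline is used.

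A reader might infer several stronger points that the article does not support:

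- *Baseline stiffness is left out.* It is not. It enters as the first repeated measurement, and the question is only how efficiently it is used.
- *Leaving out the stratification factors makes the standard errors too large.* That holds only if the factors predict the quantity analysed. The article gives no figure for this, stable effects of such factors largely cancel in a change score, and the loss may be nil.
- *The reported error bars are wrong.* The article reports mean ± SD, a descriptive summary that does not depend on the model.
- *The test of the primary outcome is the group main effect, which averages baseline with week 16 and so halves the effect.* The article does not say which term is used, and an outcome worded as a difference points to change. Naming the ANCOVA coefficient would settle it.
- *The power pairs for 36 against 36 are those of the planned analysis.* They take 0.42 as a standardised mean difference and pool arms, neither of which the article states.

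**Conclusion.** The point holds as one of efficiency. For an outcome measured once before and once after treatment, the planned group-by-time test has a larger variance than a baseline-adjusted ANCOVA for any r below 1, apart from the one degree of freedom that ANCOVA spends. Over the assumed range of r from 0.3 to 0.8, ANCOVA reduces the variance by 35% down to 10%, equivalent to 54% down to 11% more patients. The gain is large at low correlation and modest at high correlation, and the article does not show where this outcome lies.

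The size rests on the assumed r, equal variances at the two visits, the reading of the two factors as group and time, and normal theory. The last is approximate for an outcome capped at 180 minutes. The power figures illustrate the effect and are not estimates of this trial's power. Including the stratification factors is justified mainly by consistency with the randomisation, and no particular gain in precision can be claimed for it.

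**What to change.** In the Statistical analysis section, make the primary analysis an ANCOVA of week-16 morning stiffness on treatment group, with baseline stiffness as covariate. Include the factors used to stratify randomisation: disease activity, pharmacological treatment, sex and age. State that the treatment comparison from this model is the test of the primary outcome. Use the same form for each secondary outcome with its own baseline.

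The cost is a change of wording and a few degrees of freedom: one for baseline and about four for the stratification factors, out of 68. No further data or patients are needed, since every variable is collected or recorded already.
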